### *Research objectives*‌‌

The present study is guided by the following objectives:

#### Primary objectives.

a. To assess the feasibility of the therapy and assessment protocol using key evaluation indicators, including recruitment rate, retention rate, and engagement rate.b. To evaluate the acceptability of the therapy, considering the following indicators: treatment credibility and client outcome expectations, engagement, and satisfaction.

#### Secondary objective.

a. To explore the outcomes of EFT for the resolution of emotional injury among the study’s participants, according to forgiveness and letting go measures (primary outcomes) and depression and quality of life (secondary outcomes).

The aim of our study is to develop a methodologically sound and effective protocol that may serve as the foundation for a subsequent randomized clinical trial (RCT) to test the efficacy of EFT for the resolution of emotional injuries related to interpersonal offenses, in individuals aged 65 and older. In essence, a feasibility study such as the one proposed here, functions as a tool to assess the viability of the main trial (RCT)—specifically in terms of recruitment, retention, measurements, and other parameters—without necessarily focusing on clinical outcomes [22,27–29].

## Method

### Study design

The present publication is a Study Protocol, in the form of a feasibility study. This feasibility protocol is a two-arm, parallel, double-blinded, RCT aimed at informing a future trial assessing the effectiveness of EFT for resolving emotional injuries in older adults (aged above 65) in the context of interpersonal offenses.

This protocol has been registered on the ClinicalTrials.gov registry with number NCT06679452 (see section Ethics approval, below, for further details). The study plans to recruit 70 participants, with half randomly assigned to the EFT intervention and the other half placed on a waiting list to begin therapy after three months, during which they will be assessed [27]. Our chosen sample size aligns with previous similar studies [30,31]. Typically, for studies with two groups, the initial sample size should be adjusted to ensure an adequate number of completers (e.g., recruiting 40 to retain 30) [30,31]. Unlike randomized controlled trials, such feasibility studies do not require power calculations for effectiveness and instead focus on practical metrics, such as the ability to recruit a specified number of participants per month [30,31] (see more below). The recruitment process (which has not yet started) is planned for 2026, contingent upon securing funding. Following the two-month recruitment period, we anticipate initiating data collection. Subsequently, after a nine-month period, we foresee the presentation of results in a third phase. Data will be collected at the beginning, midway, and end of the therapy, as well as three and six months post-therapy (follow-ups). The study follows SPIRIT guidelines and CONSORT standards [28], consistent with prior research (Table 1) [22,29].

**Table 1 pone.0345792.t001:** SPIRIT checklist.

Section/item	Item N.º	Description	Addressed on page number
Administrative Information:			
Title	1	Descriptive title identifying the study design, population, interventions, and, if applicable, trial acronym	1
Trial registration	2a	Trial identifier and registry name. If not yet registered, name of intended registry	4
	2b	All items from the World Health Organization Trial Registration Data Set	N/A
Protocol version	3	Date and version identifier	2025
Funding	4	Sources and types of financial, material, and other support	N/A
Roles and responsibilities	5a	Names, affiliations, and roles of protocol contributors	1
	5b	Name and contact information for the trial sponsor	1 [contact]
	5c	Role of study sponsor and funders, if any, in study design; collection, management, analysis, and interpretation of data; writing of the report; and the decision to submit the report for publication, including whether they will have ultimate authority over any of these activities	N/A
	5d	Composition, roles, and responsibilities of the coordinating centre, steering committee, endpoint adjudication committee, data management team, and other individuals or groups overseeing the trial, if applicable (see Item 21a for data monitoring committee)	N/A
Introduction			
Background and rationale	6a	Description of research question and justification for undertaking the trial, including summary of relevant studies (published and unpublished) examining benefits and harms for each intervention	5-6
	6b	Explanation for choice of comparators	5
Objectives	7	Specific objectives or hypotheses	5
Trial design	8	Description of trial design including type of trial (e.g., parallel group, crossover, factorial, single group), allocation ratio, and framework (e.g., superiority, equivalence, noninferiority, exploratory)	5-6
Methods: Participants, interventions, and outcomes			
Study setting	9	Description of study settings (e.g., community clinic, academic hospital) and list of countries where data will be collected. Reference to where list of study sites can be obtained.	6
Eligibility criteria	10	Inclusion and exclusion criteria for participants. If applicable, eligibility criteria for study centres and individuals who will perform the interventions (e.g., surgeons, psychotherapists)	9
Interventions	11a	Interventions for each group with sufficient detail to allow replication, including how and when they will be administered	11-15
	11b	Criteria for discontinuing or modifying allocated interventions for a given trial participant (e.g., drug dose change in terms of medication, participant request, or improving/worsening disease)	15-16
	11c	Strategies to improve adherence to intervention protocols, and any procedures for monitoring client adherence	15-17
	11d	Relevant concomitant care and interventions that are permitted or prohibited during the trial	N/A
Outcomes	12	Primary, secondary, and other outcomes, including the specific measurement variable, analysis metric (e.g., change from baseline, final value), method of aggregation (e.g., median, proportion), and time point for each outcome. Explanation of the clinical relevance of chosen efficacy and harm outcomes is strongly recommended	5, 15-16
Participant timeline	13	Time schedule of enrolment, interventions and assessments of participants. A schematic diagram is highly recommended (see Fig 2)	11
Sample size	14	Estimated number of participants needed to achieve study objectives and how it was determined, including clinical and statistical assumptions supporting any sample size calculations	6, 11
Recruitment	15	Strategies for achieving adequate participant enrolment to reach target sample size	15-17

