### Recruitment

Client recruitment (not started yet) is planned to start in 2026, upon securing external funding. The recruitment, selection, and randomization process will be managed by an independent psychologist. Recruitment strategies include distributing posters and flyers in locations such as supermarkets, pharmacies, and senior living facilities, as well as through social media. The purpose of the recruitment posters and flyers is to inform and invite potential participants to engage in EFT, specifically targeting individuals over 65 years of age who have experienced interpersonal offenses. The central question posed will be: “Have you been the target of an injustice in the past that may still be affecting you emotionally?”

Those who express interest will be invited to a preliminary interview, conducted either in person or via phone/videoconference [29,36]. After obtaining a written consent, eligible individuals will be evaluated in a comprehensive assessment to confirm that they meet the study’s inclusion criteria. This includes administering the Structured Clinical Interview for DSM-5–Research Version (SCID-5-RV) to assess mental health conditions and MoCA to screen various cognitive domains [29,37,38].

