### Randomization

Participants will be randomly assigned to either the immediate IG or the waitlist CG using a computer-generated block randomization method to minimize bias and ensure equitable allocation between groups [22,36,39]. Randomization will be enhanced through stratification based on key participant characteristics—age, gender, educational level, and spirituality—to ensure a balanced distribution across both groups [9,29]. The CG will not receive any information about the therapy or recommendations to preserve the integrity of the CG. The allocation process will be double blinded, with group assignments concealed from both the principal investigator and the participants (Fig 2) [27,39].

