### Therapists

Sessions will be administered by psychologists with several years of psychotherapy training research and clinical practice in EFT. The first author–[name]–holds a PhD in Theology and a PhD in Psychology (specialization in Clinical Psychology), and is a psychologist with previous training in EFT [18,19,49]. The second author–[name]–is a psychologist with a PhD in Psychology (specialization in Clinical Psychology). She is a specialist in Clinical and Health Psychology, holding an advanced specialization in psychotherapy, as recognized by the National Psychologists’ Association. Furthermore, she is a certified EFT therapist and supervisor, as accredited by the International Society of Emotion-Focused Therapy (isEFT). She provides supervision and training in EFT and will serve as one of the ongoing supervisors for the team. Additionally, she has authored several scientific articles in the field [18–20].

Our therapy team will also involve two more psychologists with training in EFT, involved in the PhD program of the university. All therapists will be trained in this protocol [2] and supervised by a certified EFT supervisor. The therapists, with a commitment to avoiding any form of ageism, will be encouraged—through peer supervision—to address the key vulnerabilities, needs, and potential of this client population age group [6,15]. In addition to the four psychologists who are part of the therapy team, this research will involve another psychologist who will be responsible for the recruitment process and the assessment procedures. This psychologist—to safeguard the reliability of the evaluation results—will not be involved in the therapeutic process.

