### Ethics approval and consent to participate

The protocol is registered with number NCT06679452 on the ClinicalTrials.gov registry. It adheres to the ethical standards outlined in the Code of Ethics of the Portuguese Association of Psychologists (aligned with the American Psychological Association). This protocol was submitted to and received approval from the Ethics Committee of the University of Maia (under the reference number 40/2022). Participants will be fully informed about the study’s context, goals, and methodologies before giving written informed consent to participate. Participation will be voluntary, and participants can withdraw at any time and request a summary of the findings, upon their participation.

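### The trial is labelled double-blinded although participants and therapists must know the arm, and one psychologist manages recruitment and randomisation and also assesses

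*Protocol article*

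**What the plan says.** **Blinding.** Study design describes the whole trial: "This feasibility protocol is a two-arm, parallel, double-blinded, RCT". Randomization is more specific: "The allocation process will be double blinded, with group assignments concealed from both the principal investigator and the participants".

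**Comparator.** Study design has "the other half placed on a waiting list to begin therapy after three months, during which they will be assessed". The immediate arm is offered twelve weekly in-person sessions (Therapy). No sham or attention control is described.

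**Who does what.** Recruitment states "The recruitment, selection, and randomization process will be managed by an independent psychologist". Therapists describes a therapy team of four psychologists, presents the first and second authors under that heading, and then adds "another psychologist who will be responsible for the recruitment process and the assessment procedures", who takes no part in therapy. Data collection has the independent psychologist carry out the initial assessment and the final qualitative interview.

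**Information to participants.** Randomization says "The CG will not receive any information about the therapy or recommendations to preserve the integrity of the CG". Ethics approval says "Participants will be fully informed about the study’s context, goals, and methodologies before giving written informed consent to participate".

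**The concern.** Two protections are claimed or implied that the design does not deliver.

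The first is blinding of participants. A person who begins weekly therapy and a person told to wait three months cannot both be unaware of their group. If the label stands, readers will credit the forgiveness, letting go, quality of life and depression results with a protection against expectancy effects that they lack. The planners of the later efficacy trial may carry the label forward.

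The second is separation of roles. The person who decides who is eligible should not be able to learn the next assignment, and an assessor described as independent should ideally not know the arm. Here one psychologist appears to manage every step from recruitment to assessment. If that person could see upcoming assignments, eligibility decisions that need judgement could be influenced by them. One example is whether a psychiatric disorder would require a marked departure from the treatment protocol.

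**Working it through.** No arithmetic applies: the article gives no figure on this point, and none is needed. The check sets the statements side by side.

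1. **Can participants be blind?** Inputs: immediate weekly in-person therapy (Therapy); a three-month wait (Study design); full information on methods before consent (Ethics approval). A consenting participant knows that the two options are therapy now or therapy later, and sees which one occurs. Participant blinding after assignment is therefore impossible under the document's own design.

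2. **Can therapists be blind?** They deliver the sessions, so no. The principal investigator, whom Randomization lists as blind, is not identified. The first and second authors are both described under Therapists. If either is the principal investigator and treats participants, that part of the claim fails too. This is conditional, because the article does not say.

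3. **Which outcomes are affected?** Exploratory outcomes lists four scales. EFI and the Letting Go Measure are described as self-report. WHOQOL-OLD and GDS-15 are item questionnaires answered by the participant. That is four of four.

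4. **Is the independent psychologist separate from allocation?** Recruitment gives an independent psychologist recruitment, selection and randomisation. Therapists gives recruitment and assessment to the one further psychologist outside the therapy team. Data collection gives the same independent psychologist the initial assessment and final interview. Recruitment is common to the first two, and only one such person is described, so the natural reading is a single person. The only independence stated is from therapy. No other person is named for allocation or assessment.

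5. **When is baseline taken?** Data collection introduces its three assessment points, including the one before therapy, as following assignment to groups. As written, even the baseline scales may be answered with the arm known.

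6. **Does the article say otherwise elsewhere?** The Abstract describes a two-arm, parallel-group randomised trial with a waiting-list control and makes no blinding claim. The limitations in the Discussion cover sample size, follow-up length and group uniformity, but not unblinded self-report.

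**The case against.** The strongest reply is that the Randomization sentence has the allocation process as its subject. It can fairly be read as concealment up to the moment of assignment, which is feasible. That reading is available, and it suggests loose terminology rather than a false masking scheme. It does not rescue Study design, which applies the label to the whole trial.

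It is also fair that little of the planned inference depends on blinding. Outcomes are summarised without formal hypothesis tests, the article disclaims establishing causality, and the later trial's sample size will not be based on this study's estimates. Progression criteria are thresholds on scores and rates, not contrasts between arms. This lowers the severity but does not make the label correct.

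On assessment, questionnaires come back in sealed envelopes and the scales are answered by participants, so the psychologist's knowledge of the arm has limited reach. The final interview asks about change during therapy and could hardly be blinded. Both points stand.

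A reader might be tempted to infer more than the text supports:

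- **That nobody is blind.** The article is silent on the data analyst, and silence is not evidence of unblinding.
- **That the recruiting psychologist holds the list.** The text says this person manages randomisation and that the method is computer-generated and blocked. It does not say who generates or keeps the sequence.
- **That a given share of assignments is predictable.** No block size is stated, so no share can be calculated from the document.
- **That the statement about controls contradicts consent.** It can mean that therapy content is withheld during the wait. The wording needs clarifying, but a contradiction is not established.
- **That the registry entry is wrong.** Only the registration number is given.

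**Conclusion.** The point holds at moderate severity. That participants and therapists know the arm follows directly from the design, so the double-blinded label is wrong and all four exploratory scales are unblinded self-report. The size of any resulting bias cannot be estimated from the document.

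The second part rests on reading the psychologist in Recruitment, Therapists and Data collection as one person. On that reading, the text does not secure allocation concealment or assessor blinding. It does not show that either has been breached.

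Recruitment, retention and questionnaire completion rates are little affected. The correction matters mainly because the stated aim is a methodologically sound protocol on which a later efficacy trial can be built.

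**What to change.** - **Study design:** replace the term double-blinded with *open-label (participants and therapists aware of allocation)*.
- **Randomization, concealment:** limit the sentence to concealment of the sequence until assignment.
- **Custody of the sequence:** have it generated and released by an existing team member who neither enrols nor assesses, or by an online randomisation tool.
- **Timing:** reveal each assignment only after eligibility and baseline measures are complete, and reorder the Data collection text to match.
- **Randomization, controls:** if the statement about withholding information refers to therapy content during the wait, say so.
- **Discussion:** add unblinded self-report to the limitations.
- **Registry:** check that the masking entry agrees with the corrected text.

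The cost is a less favourable design label and the reassignment of one small task. No extra staff or participants are needed. Recruitment has not started, so the change can be made before anyone is enrolled.

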**Methods: Assignment of interventions (for controlled trials)**			
Allocation:			
Sequence generation	16a	Method of generating the allocation sequence (e.g., computer-generated random numbers), and list of any factors for stratification. To reduce predictability of a random sequence, details of any planned restriction (e.g., blocking) should be provided in a separate document that is unavailable to those who enroll participants or assign interventions	11
Allocation concealment mechanism	16b	Mechanism of implementing the allocation sequence (e.g., sequentially numbered, opaque, sealed envelopes), describing any steps to conceal the sequence until interventions are assigned	11
Implementation	16c	Who will generate the allocation sequence, who will enrol participants, and who will assign participants to interventions	11
Blinding (masking)	17a	Who will be blinded after assignment to interventions (e.g., trial participants, care providers, outcome assessors, data analysts), and how	11
	17b	If blinded, circumstances under which unblinding is permissible, and procedure for revealing a participant’s allocated intervention during the trial	11
**Methods: Data collection, management, and analysis**			
Data collection methods	18a	Plans for assessment and collection of outcome, baseline, and other trial data, including any related processes to promote data quality (e.g., duplicate measurements, training of assessors) and a description of study instruments (e.g., questionnaires, laboratory tests) along with their reliability and validity, if known. Reference to where data collection forms can be found, if not in the protocol	10, 15-16
	18b	Plans to promote participant retention and complete follow-up, including list of any outcome data to be collected for participants who discontinue or deviate from intervention protocols	15-17
Data management	19	Plans for data entry, coding, security, and storage, including any related processes to promote data quality (e.g., double data entry; range checks for data values). Reference to where details of data management procedures can be found, if not in the protocol	16
Statistical methods	20a	Statistical methods for analysing primary and secondary outcomes. Reference to where other details of the statistical analysis plan can be found, if not in the protocol	17-18
	20b	Methods for any additional analyses (e.g., subgroup and adjusted analyses)	N/A
	20c	Definition of analysis population relating to protocol non-adherence (e.g., as randomised analysis), and any statistical methods to handle missing data (e.g., multiple imputation)	13-14, 18
**Methods: Monitoring**			
Data monitoring	21a	Composition of data monitoring committee (DMC); summary of its role and reporting structure; statement of whether it is independent from the sponsor and competing interests; and reference to where further details about its charter can be found, if not in the protocol. Alternatively, an explanation of why a DMC is not needed	16
	21b	Description of any interim analyses and stopping guidelines, including who will have access to these interim results and make the final decision to terminate the trial	18
Harms	22	Plans for collecting, assessing, reporting, and managing solicited and spontaneously reported adverse events and other unintended effects of trial interventions or trial conduct	17-18
Auditing	23	Frequency and procedures for auditing trial conduct, if any, and whether the process will be independent from investigators and the sponsor	17-18
**Ethics and dissemination**			
Research ethics approval	24	Plans for seeking research ethics committee/institutional review board (REC/IRB) approval	16, 18
Protocol amendments	25	Plans for communicating important protocol modifications (e.g., changes to eligibility criteria, outcomes, analyses) to relevant parties (e.g., investigators, REC/IRBs, trial participants, trial registries, journals, regulators)	18
Consent or assent	26a	Who will obtain informed consent or assent from potential trial participants or authorised surrogates, and how	18
	26b	Additional consent provisions for collection and use of participant data and biological specimens in ancillary studies, if applicable	N/A
Confidentiality	27	How personal information about potential and enrolled participants will be collected, shared, and maintained in order to protect confidentiality before, during, and after the trial	16,18
Declaration of interests	28	Financial and other competing interests for principal investigators for the overall trial and each study site	N/A
Access to data	29	Statement of who will have access to the final trial dataset, and disclosure of contractual agreements that limit such access for investigators	18
Ancillary and post-trial care	30	Provisions, if any, for ancillary and post-trial care, and for compensation to those who suffer harm from trial participation	N/A
Dissemination policy	31a	Plans for investigators and sponsor to communicate trial results to participants, healthcare professionals, the public, and other relevant groups (e.g., via publication, reporting in results databases, or other data sharing arrangements), including any publication restrictions	18
	31b	Authorship eligibility guidelines and any intended use of professional writers	N/A
	31c	Plans, if any, for granting public access to the full protocol, participant-level dataset, and statistical code	N/A
